# Addressing mental health problems among persons without stable housing in the context of the COVID-19 pandemic: study protocol for a randomised trial. RESPOND – France

**DOI:** 10.1186/s12889-023-17238-7

**Published:** 2023-11-17

**Keywords:** Randomized controlled trial, Psychological distress, COVID-19, Housing instability, Migrant, Doing what matters in times of stress, Problem management plus, Economic evaluation, France

## Abstract

**Background:**

The COVID-19 pandemic has had an impact on population-wide mental health and well-being. Although people experiencing socioeconomic disadvantage may be especially vulnerable, they experience barriers in accessing mental health care. To overcome these barriers, the World Health Organization (WHO) designed two scalable psychosocial interventions, namely the web-based Doing What Matters in Times of Stress (DWM) and the face-to-face Problem Management Plus (PM+), to help people manage stressful situations. Our study aims to test the effectiveness of a stepped-care program using DWM and PM + among individuals experiencing unstable housing in France – a majority of whom are migrant or have sought asylum.

**Methods:**

This is a randomised controlled trial to evaluate the effectiveness and cost effectiveness of a stepped-care program using DWM and PM + among persons with psychological distress and experiencing unstable housing, in comparison to enhanced care as usual (eCAU). Participants (N = 210) will be randomised to two parallel groups: eCAU or eCAU plus the stepped-care program. The main study outcomes are symptoms of depression and anxiety measured using the Patient Health Questionnaire Anxiety and Depression Scale (PHQ-ADS).

**Discussion:**

This randomised controlled trial will contribute to a better understanding of effective community-based scalable strategies that can help address the mental health needs of persons experiencing socioeconomic disadvantage, whose needs are high yet who frequently have limited access to mental health care services.

**Trial registration:**

this randomised trial has been registered at ClinicalTrials.gov under the number NCT05033210.

**Supplementary Information:**

The online version contains supplementary material available at 10.1186/s12889-023-17238-7.

## Background

The COVID-19 pandemic has contributed to a worldwide increase in the prevalence of psychological distress and symptoms of anxiety and depression, [1] although this has recently been a matter of some debate, in part due to heterogeneity in findings across different stages of the sanitary crisis [2]. While in the general population the increase in mental health problems was observed in 2020 and appears to have decreased afterwards, this may not be the case in marginalized groups. In particular, research has highlighted a high prevalence of mental health problems among individuals experiencing socioeconomic disadvantage compared to the general population [3, 4]. Mental health care systems are thus facing difficulties in addressing this growing demand, which may result in delays or unmet needs, increasing existing social inequalities in mental health and health care access [5].

In France in recent years, and more particularly in the Paris area, there has been an increase in the number of people who are homeless, sleeping rough or experience unstable housing conditions, among whom a large proportion are recent migrants and asylum seekers due in part to changes in migratory patterns and asylum regulations which contribute to newcomers’ social vulnerability [6]. In addition to social disadvantage, this group often experiences violence, discrimination, and isolation, as well as cultural and language barriers before, during and after migration, [7] and should have priority in terms of prevention of health conditions and treatment. However, this group experiences widely documented unmet needs in terms of mental health care. The COVID-19 pandemic has resulted in increased difficulties in accessing mental health care at large and in marginalized populations, calling for the evaluation of new scalable psychosocial interventions.

To make mental health care accessible, it is necessary to adapt it. For that purpose, the World Health Organization (WHO) has developed a number of scalable psychological interventions based on Acceptance and Commitment Therapy (ACT) including Doing What Matters in Times of Stress (DWM) [8] and Problem Management Plus (PM+) [9]. DWM is a self-help stress management guide that includes pre-recorded audio exercises and illustrations, introducing participants to five different strategies to relieve stress (e.g. mindfulness exercises) and has been shown to reduce psychological distress across multiple trials [10, 11]. To be widely accessible, DWM has been adapted for individual use as a mobile-supported website with distance support by a trained person spread over the course of 5 weeks. Self-Help + (SH+), is an intervention based on the DMW manual. The PM + intervention is based on principles of Cognitive Behavioural Therapy (CBT) and Problem-Solving Therapy and can be delivered by non-specialists in situations where mental health care is not accessible. PM + has four core features: it is brief (five sessions); delivered by non-specialist helpers; transdiagnostic (it addresses depression, anxiety, post-traumatic stress disorder, psychological distress); it was originally designed for individuals living in communities with limited mental health care resources but is easily adaptable to different populations, cultures and languages. Organised in 5 sessions, PM + can be delivered individually or in groups of adults experiencing distress to help them develop problem management strategies. Both individual and group formats of PM + have been shown to reduce anxiety and depression [12, 13].

These interventions do not replace specialised mental health care for people with severe psychiatric disorders, but contribute to reducing psychological distress and decrease later risk of mental disorders among persons with mild to moderate manifestations.

The main aim of the present randomised controlled trial (RCT) is to evaluate the effectiveness of the stepped-care program combining DWM and PM + to reduce symptoms of depression and anxiety amongst adults experiencing unstable housing in comparison to enhanced care-as-usual (eCAU). The secondary objectives are to evaluate:*(a)* the effect of the intervention on participants’ quality of life and resilience; *(b)* the moderation of the effect of the intervention by participants’ socio-demographic characteristics, living conditions, and experiences of trauma (i.e. individuals who have lower levels of education, less stable housing situation, and higher levels of trauma are expected to benefit less from the psychosocial program being tested);*(c)* the resource impacts and cost-effectiveness of DWM and PM + interventions. In France, a large proportion of individuals experiencing unstable housing conditions and sheltered in collective accommodation facilities are migrants [6], therefore the DWM and PM + protocols were professionally translated and back translated by study helpers who are native speakers and trained translators to languages most frequently spoken by recent asylum seekers and migrants to France (Dari and Pashto); we also used the existing Arabic translation provided by the WHO [14]. The study being conducted under the supervision of a psychiatrists (AT), the validity of the tools used to screen for psychological distress can be validated after the trial. PM + was previously used in studies conducted across different parts of the world (for instance in Pakistan and among Syrian refugees to Jordan) [12, 15]. Prior to the implementation of this randomised controlled trial, we conducted a pilot study in 2019–2020 to test the feasibility of recruiting participants for this intervention among people who do not speak French and reside in temporary accommodation. The pilot study allowed us to make a number of adjustments to study recruitment procedures (for instance the selection of participating accommodation centres) and research questionnaires, as well as estimate attrition. The presentRCT is part of the Horizon 2020 cross-national RESPOND project (Australia, Belgium, France, Germany, Italy, Netherlands, Spain, Sweden and the United Kingdom) aiming to test effective ways of addressing population mental health needs following the COVID-19 pandemic [16, 17]. This protocol was not peer-reviewed as part of the funding process.

## Methods: participants, intervention and outcomes

### Study setting

This study is set in the Paris and Caen regions in France, among people who experience unstable housing conditions (that is individuals who are homeless and are sheltered in temporary accommodation, by other people, or have no regular shelter) recruited via temporary accommodation centres as well as ambulatory care for people who experience social disadvantage and/or are migrant. The Paris region traditionally attracts new migrants because it concentrates economic resources. As a result, it a region where many infrastructures serve migrants – particularly those experiencing social disadvantage, making recruitment easier. As for Caen, it has also become an area concentrating migrants, due to its proximity to the UK. Moreover, one of the study’s collaborators ([name]) is based in Caen. We acknowledge that the selection of study locations may be a limitation of the protocol.

### Eligibility criteria

Individuals will be able to participate in the trial if they are 18 years of age or older, have elevated levels of psychological distress as assessed with the Kessler-10 scale (K10 score ≥ 15.9) [18], speak one of the study languages (Arabic, Dari, French, Pashto), find themselves without stable housing and are willing to participate.

Exclusion criteria include having an acute medical or psychiatric condition requiring urgent medical attention (e.g. hospitalization) as ascertained by the consultant psychiatrist involved in the trial ([name]), a high risk of suicide, moderate/severe cognitive impairment (e.g. severe intellectual disability or dementia), being under legal protection (guardianship, curatorship, safeguard of justice), a change in the level of psychotropic treatment in the two months preceding the trial (as ascertained in the baseline study questionnaire at T1), and refusal to participate.

### Interventions

This is a randomized controlled study, comparing a stepped-care intervention to enhanced Care as Usual (all participants will receive Psychological First Aid, PFA, prior to treatment allocation). All study assessments and interventions are described in Fig. 1. Participants randomly allocated to the intervention arm through the electronic platform used to collect study data will first receive the DWM intervention for 5 weeks (weeks 2 to 6). At the end of the DWM intervention, participants will complete the first follow-up questionnaire (T2 - week 7), which includes the K10 scale to evaluate whether they still experience high levels of psychological distress (K10 score ≥ 15.9). If so, they will receive the PM + intervention for the next 5 weeks (weeks 8 to 12) and then answer the second follow up questionnaire (T3 - week 13). Otherwise, they will skip the PM + intervention and only complete a follow-up questionnaire at week 13. Two months later, participants will complete the last follow-up questionnaire (T4 - week 21).

Participants allocated to the control group will complete the study questionnaires (T1, T2, T3 and T4) at the same time points as the intervention group and will not receive the DWM/PM + stepped-care program. The control group consists of enhanced Care as Usual, as participants receive Psychological First Aid (PFA) in addition to standard treatment.

Psychological First Aid (PFA) is a support strategy that involves humane, supportive and practical help for individuals experiencing a serious collective crisis [19] delivered to all study participants in both trial arms. PFA consists of a conversation (approximately 30–45 min) which can be provided remotely (e.g. videoconferencing or telephone). This conversation has various themes; non-intruding practical care and support, description of mental health needs and concerns, information about ways of addressing individuals’ basic needs, provision of comfort and help staying calm, help connecting to services and social support, as well as protection of individuals from further harm [20].Doing What Matters in times of stress (DWM) is a self-help stress management guide based on the principles of Acceptance and Commitment Therapy (ACT). DWM includes five sections, each of which focuses on a specific skill (Grounding; Unhooking; Acting on your values; Being kind; Making room). In this study, DWM will be delivered online, via a web-based program designed to be used on a smartphone with the assistance of a helper. Helper support will be flexible, and on average occur once a week for approximately 15–20 min. Every week over the course of five weeks, a new module will be unlocked.Problem Management + (PM+) is a brief, psychological intervention based on cognitive behavioural therapy (CBT) techniques that are empirically supported, formally recommended and developed by the WHO. The manual involves the following empirically supported elements: problem solving, stress management, behavioural activation, and accessing social support. In 60-minute sessions, participants talk to trained non-professional helpers. PM + sessions will be conducted face-to-face by a helper, also over a five-week period at a rate of one session per week.

The cultural acceptability of DMW and PM + among potential study participants and social workers attending to their needs was verified in qualitative research prior to study inception.

For both DWM and PM+, manuals can be accessed online [8, 9].

**Fig. 1 Fig1:**
[figure not shown]
Framework of the RESPOND trial – France

### Study outcomes

Table 1 shows all the measures collected across study questionnaires (from T1 to T4).

The primary study outcome is the Patient Health Questionnaire-Anxiety and Depression Score (PHQ-ADS), a sum of scores on the Patient Health Questionnaire-9 (PHQ-9) and the Generalized Anxiety Disorder − 7 (GAD-7), two scales evaluating respectively symptoms of depression and of generalised anxiety disorder [21, 22]. The PHQ-9 includes 9 items and the GAD-7 comprises 7 items, the combined score ranging from 0 to 48. Elevated scores indicate a higher level of symptoms of depression and anxiety. Two validation studies of the PHQ-ADS among patients with chronic pain and cancers have been summarized and published [22]. This score has strong internal reliability (Cronbach’s alpha of 0.8 and 0.9), strong convergent validity, sufficient uni-dimensionality and is sensitive to change.

As secondary study outcomes, we will use the PHQ-9 alone [23], the GAD-7 alone [24], as well as other measures of participants’ mental health: the Patient Checklist-5 (PCL-5) assessing symptoms of Post-Traumatic Stress Disorder [25], Psychotic Symptoms assessed using the MINI questionnaire [26] and quality of life assessed using the EQ-5D-5 L [27]. Additionally, we will assess outcome-based resilience, which is operationalised as the individual deviation from the sample-based normative stressor reactivity, that is a difference between individual-level observed and sample-based predicted values of psychological distress considering a certain number of stressors. Resilience will be calculated with a measure of stressor exposure which has been adapted from the Mainz Inventory of Microstressors(MIMIS) and the PHQ-9 and GAD-7 [28].

Additionally, baseline and follow-up study questionnaires will ascertain participants’ sociodemographic characteristics (sex, age, nationality, educational level, income, etc.), as well as COVID-19-related stressors (that is 11 items relative to worries regarding COVID-19 infection and possible stigma due to contamination, as well as loss of income, employment or basic life resources due to COVID-19 and possible administrative complications related to the sanitary crisis and its aftermath). Furthermore, participants are asked to report on their appraisal style using the Perceived Positive Appraisal Style Scale, content-focused version (PASSc) [28]. Moreover participants’ stress levels will be assessed using the Brief Trauma Questionnaire (BTQ) [29]. Finally, cost-effectiveness of the intervention will also be examined.

### Participant timeline

Each participant will be in the study for 21 weeks.

### Sample size

Overall, 210 participants will be included. Based on previous studies of PM+ [30, 31], we aim to detect a small to medium effect size corresponding to a Cohen’s d = 0.4 in the intervention group at 2 months, as measured with the PHQ-ADS and as compared to the control group. A calculation of statistical power for a repeated measures study design (mixed regression model), given incomplete participation in each of the planned assessments, suggests a minimum sample size of n = 73 per group (power = 0.80, alpha = 0, 05, bilateral, rho = 0.9). Considering an attrition rate of 30%, estimated based on a prior pilot study and past evaluations of PM+, we calculated a total number of 210 participants needed (105 in each group). If needed, missing data on study covariates will be handled using standard multiple imputation techniques.

### Recruitment

Participants are recruited directly in temporary accommodation centres as well as ambulatory care for people experiencing social disadvantage and/or who are migrant, by trained helpers who are in contact with each site’s coordinator and regularly visit to list potential participants and contact them. Recruitment and allocation started in March 2022 and is should be completed by the end of October, 2023. The first post-allocation took place in July 2022 and the last one will take place in February 2024, study close-out should occur in February 2024. To enhance retention and reduce study drop-out, participants are compensated 3*20 euros (at T1, T3 and T4). We also cover their travel expenses if they are interviewed on research premises rather than at the accommodation centre where they live.

### Adverse events

Any undesirable experience occurring during the study, whether or not considered related to the trial procedure or the stepped-care DWM/PM + program, will be considered an Adverse Event. All adverse events reported spontaneously by study participants or observed by the investigators will be recorded and reported to the promoting agency (ANRS-MIE).

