### Data management

Quantitative data obtained from study questionnaires being collected on an eCRF will be automatically stored electronically. Each participant will be identified with a unique numerical identifier, all personal data used to contact participants being stored separately and securely. In compliance with French regulations, all data will be stored for two years after the end of the trial. In case of adverse events, information will be systematically collected, forwarded to the promoting agency and if necessary participation will be stopped. The trial will be audited after completion.

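### Adverse events are recorded by spontaneous report or observation, with about 8 or 13 planned post-allocation contacts in the programme arm against 3 in controls, so these counts cannot be fairly compared between arms

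*Protocol article*

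**What the plan says.** The Adverse events section defines an event broadly: "Any undesirable experience occurring during the study, whether or not considered related to the trial procedure". Relatedness plays no part, so the definition covers controls as much as programme participants. It then says how events enter the record: "All adverse events reported spontaneously by study participants or observed by the investigators will be recorded". The Data management section adds "In case of adverse events, information will be systematically collected, forwarded to the promoting agency". That sentence opens with the condition that an event has occurred, so it governs what happens once an event is known, not how it is found. Table 1 lists no adverse-event question.

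On contacts, the Interventions section says of DWM: "Helper support will be flexible, and on average occur once a week for approximately 15–20 min", over five weeks. Of the second step it says: "PM + sessions will be conducted face-to-face by a helper, also over a five-week period at a rate of one session per week". Only participants still at or above the K10 threshold at T2 go on to PM+. Controls "complete the study questionnaires (T1, T2, T3 and T4) at the same time points as the intervention group" and have no part of the programme. PFA is given to everyone before allocation, so it adds no post-allocation contact in either arm. The section on assignment of the intervention says that neither participants nor data collectors can be blinded.

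**The concern.** Under passive recording, an event is captured only if there is an occasion on which it can be mentioned or noticed. Here the number of such occasions is set by the allocated arm. The additional ones are supportive conversations with a helper about the participant's difficulties, where an undesirable experience is likely to come up. The PM+ contacts go only to participants with persisting distress, while equally distressed controls gain no contact.

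At stake is how the safety record is read. Events go to the promoting agency, and participation can be stopped because of them. Counts by arm from a randomised trial will naturally be read as a comparison, whether or not a test is planned. An excess in the programme arm could then reflect more listening, not more harm, and events in controls that fall outside the scheduled instruments could be missed. The primary outcome is not affected.

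**Working it through.** The article gives neither an expected adverse-event rate nor a total number of contacts, so there is no stated figure to reproduce. The contacts come from the schedule. The size of the effect needs assumptions, which are labelled as such.

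**Planned post-allocation contacts (Interventions section)**
- Control: T2 (week 7), T3 (week 13), T4 (week 21) = 3.
- Programme, DWM only: 3 + 5 (weeks 2 to 6) = 8, or 8/3 = 2.7 times control.
- Programme, DWM and PM+: 3 + 5 + 5 (weeks 8 to 12) = 13, or 13/3 = 4.3 times control.

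The five DWM contacts are an average, so 8 and 13 are approximate.

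**Assumptions (not in the documents)**
- Equal true event rates in both arms.
- Onset uniform over weeks 1 to 21, a span of 20 weeks.
- Each contact after onset independently brings the event to light with probability p = 0.05, 0.10 or 0.20.

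**Formula.** An event with k contacts still to come is recorded with probability 1 − (1 − p)^k. Average this over the onset week.
- Control: k = 3 for 6 weeks (1 to 7), k = 2 for 6 weeks (7 to 13), k = 1 for 8 weeks (13 to 21).
- DWM only: k = 8, 7, 6, 5, 4, 3 for one week each (1 to 7), then k = 2 for 6 weeks and k = 1 for 8 weeks.
- DWM and PM+: k = 13, 12, …, 2 for one week each (1 to 13), then k = 1 for 8 weeks.

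Control at p = 0.10: (6 × 0.271 + 6 × 0.190 + 8 × 0.100) / 20 = 3.566 / 20 = 0.178.

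| p | Control | DWM only | DWM and PM+ | Ratio to control |
|---|---|---|---|---|
| 0.05 | 9.2% | 12.2% | 20.5% | 1.33 to 2.23 |
| 0.10 | 17.8% | 22.6% | 34.9% | 1.27 to 1.96 |
| 0.20 | 33.4% | 39.4% | 53.1% | 1.18 to 1.59 |

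The ratio for the whole programme arm lies between the two ends of each range, depending on the share stepped up to PM+, which the article does not give.

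**Sensitivity**
- Short recall: if an event is mentioned only within 4 weeks of onset, each control visit covers the 4 weeks before it. That is 12 of 20 weeks with k = 1, a recorded share of 0.6p. The ratios rise to 2.1 to 3.6 (p = 0.05), 2.0 to 3.4 (p = 0.10) and 1.8 to 3.0 (p = 0.20).
- Near-complete reporting: at p = 0.80 with unlimited recall, the shares are 91%, 91% and 92%, a ratio of about 1.0. With 4-week recall the ratio is still 1.3 to 1.6.

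**Effect of the fix.** Data from T2, T3 and T4 alone rest on 3 occasions in each arm.

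**The case against.** The strongest objection is that harm is also measured actively. Table 1 schedules the step-by-step suicidality screen, MINI psychotic symptoms, PHQ-9, GAD-7, PCL-5 and the CSRI at T1 to T4, and controls follow the same time points. A reader might infer that every harm comparison in this trial is biased, or that self-harm and admissions in controls would simply go unseen. The documents do not support either inference. Comparisons on these instruments rest on 3 follow-up assessments per arm, and what those visits reveal may also count as observed by the investigators, although the article does not say how they feed the adverse-event record. This objection stands and limits the point to passively recorded events.

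Second, no between-arm comparison of adverse events appears among the objectives, outcomes or statistical methods. That also stands: the bias is a risk if the counts are compared, not a flaw in a stated analysis.

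Third, a reader might apply 1 − (1 − p)^k with k = 3, 8 and 13 directly, which gives ratios of 1.7 to 3.4 for the same p. That credits every event with every contact, as though all events began straight after allocation. For onset after week 12, which is 9 of the 20 weeks, the remaining contacts are identical in both arms. Allowing for timing gives 1.2 to 2.2.

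Fourth, the article is condensed: form wording and visit prompts may sit in the full protocol, Table 1 lists measures and need not show every prompt, and the rule does not say that no other route is used. This is fair as a caution. But the article does more than leave the method open: it names one, and that method is passive.

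Finally, timing. Recruitment was due to end in October 2023, the article appeared on 17 November 2023, and the last assessments were due in February 2024. A new question reaches only the remaining visits. This stands for the question but not for the table rule.

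**Conclusion.** The point holds in limited form. As the article describes it, adverse-event capture depends on contacts that differ by arm: 3 in controls against about 8 or 13 in the programme arm, in an unblinded trial. Passively recorded counts therefore cannot be fairly compared between arms. With equal true rates, the programme arm would show about 1.2 to 2.2 times as many recorded events if onset is uniform over weeks 1 to 21, the chance of mention is 5% to 20% per contact and recall is unlimited. The ratio is larger if recall is short and close to 1 only if nearly every event is eventually mentioned. The direction follows from the schedule. The size rests on probabilities that the documents do not give.

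Harm measures taken in both arms at T2 to T4 are not affected by this contact imbalance. The point deserves correction before analysis because the remedy is cheap, but it does not bear on the primary outcome.

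**What to change.** 1. Before analysis, fix the rule that any between-arm harm comparison uses only data from the common T2, T3 and T4 visits: the suicidality screen, MINI psychotic symptoms, worsening on PHQ-9, GAD-7 and PCL-5, and CSRI service use, all already collected.
2. List events that came to light at DWM or PM+ contacts separately, by source, and do not present them as a between-arm count.
3. Where visits remain, ask one identically worded adverse-event question in both arms at T2, T3 and T4. Report the answers separately from earlier passive reports, so that two methods of ascertainment are not mixed.
4. If the full protocol or the eCRF already prompts for adverse events at these visits, say so in the Adverse events section; step 3 is then unnecessary.

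Cost: steps 1 and 2 cost almost nothing and need no new data. Step 3 means one eCRF item in four languages (Arabic, Dari, French, Pashto) and an amendment, which under the Ethics and dissemination section is notified to the ethics committee with authorisation sought. It will also bring in more non-serious events, and it can reach only participants with visits still to come.
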